**Methods and analysis:**

A prospective open cohort study between 1 January 2002 and 30 September 2014 will be based on the general population of people prescribed statins, using records from UK general practices contributing to the Clinical Practice Research Database (CPRD). Participants aged 25–84 years will enter the cohort on the date of their first prescription for a statin and leave on the earliest date of: a cardiovascular event; death; leaving the practice; the last practice upload date or the study end date. If there are no prescriptions within 90 days after the expected finishing date of a prescription, a patient will be defined as a stopper with the discontinuation outcome date as the expected finishing date. Rates of statin discontinuation will be calculated by calendar year, type and dose of statin, age, and morbidities. Cox proportional regression analyses will be run to identify the most important factors associated with discontinuation. Analyses will be run separately for patients without CVD (primary prevention) and with diagnosed CVD (secondary prevention).

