### Sample selection

This will be a prospective open cohort study of new statin users identified during the study period between 1 January 2002 and 30 September 2013. Incident cases who discontinued statin therapy will be identified during follow-up. Patients will enter the cohort on the date of their first recorded statin prescription within the study inclusion period. Patients will be followed up until the earliest of: death; deregistration with the practice; last upload of computerised data; 1 year from the date the study inclusion period ended. Patients will be subdivided into two groups evaluated on the date when they started taking statins: those without CVD records before the entry date (taking statins for primary prevention); those with CVD diagnosed at or before entering the study (taking statins for secondary prevention). Patients without CVD at the baseline date will be followed up until the time of a CVD diagnosis if it occurs before the study exit date.

We expect the rate of discontinuation to be lower in the secondary prevention group, and this subdivision will make our results more easily comparable with existing studies.

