### Inclusion criteria

Eligible patients will be aged 25–84 years at the study entry, have at least two prescriptions for a statin in the study period and have at least 1 year of records prior to entry—calculated from the later date of: the date of registering with a general practice or the earliest date of upload of computerised practice data—and at least 1 year of follow-up—calculated from their first statin prescription in the study period. Patients with one or more prescriptions for statins in the 12 months prior to cohort entry will be excluded. Cerivastatin will not be included in the study because it was withdrawn from the market in August 2001, but patients with prescriptions for it in the 12 months prior to cohort entry will be excluded.

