### Statistical analysis

All analyses will be performed separately for the subgroups with and without a diagnosis of CVD at the study entry date.

The numbers of incident users who stop statins will be reported and the rate of discontinuation will be assessed by dividing the number of incident stoppers by the number of person-years. The rates will be calculated overall and by calendar year, ethnic group, deprivation quintile, initial statin type, and baseline risk of CVD (for primary prevention group). We shall also calculate the percentages of patients who switch between different statins during the study period, considering a patient as a switcher if their type of statin (ingredient) changed during their follow-up. For patients in the primary prevention group who were diagnosed with CVD after entering the study, we shall report the percentages of patients who continued using statins after the diagnosis.

We shall report general descriptive statistics such as average duration of statin therapy before discontinuation, proportions of patients who had their last statin prescription within 6 months, 6 months to 1 year, 1–5 years or more than 5 years after their first prescription, and graphically summarise the data using Kaplan-Meier curves. As we expect different rates of discontinuation for short-term (less than 12 months between the first and the last prescription) and long-term (more than 12 months between the first and the last prescriptions) users, we shall calculate rates by term of use.

For those patients who discontinued statins and for those who did not, summary statistics will be calculated for the baseline covariates. We shall report frequencies and proportions for categorical data, and for continuous data, suggested bands as well as means (SD), medians and ranges. We shall also report the type of statin, the potency, calendar year for the baseline, cumulative duration of exposure before leaving the cohort (defined as the time interval between the first prescription and expected end date for the last prescription), and whether the patient had switched statin type during the study period. We shall calculate the survival-time function, report the descriptive statistics such as median duration, plot Kaplan-Meier curves for the covariates and compare the survivor functions for the covariates using the log-rank test.

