### Additional analyses

Patients might discontinue statins within the first year or after a longer period. The characteristics of these patients might differ, so we shall rerun the main analysis twice, in the first censoring all patients who did not discontinue before the end of year one, and in the second removing all patients who did discontinue before the end of year 1.

Some statin users have discontinuous use, with one or more restarts against a background of fairly continual usage. We shall define a subcohort in the study period for patients who discontinued statins (the outcome date in the main analysis will be their new entry date) and follow them until they have a new statin prescription or they are censored as described in the Study design section. We shall describe how many people restarted statin therapy within the first 6 months, 7–12 months and 12 or more months after their new entry dates using Kaplan-Meier estimates. We shall report descriptive statistics for the covariates listed above both for stoppers who restarted and those who did not.

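### The share of stoppers who restart statins is to be read from Kaplan-Meier estimates that censor deaths, which overstates restarting, mainly beyond 12 months

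*Protocol article*

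**What the plan says.** **Restarting.** Under Additional analyses, patients who stopped form a subcohort whose clock starts at the discontinuation date. They are followed to a new statin prescription or to censoring. The stated output is: "We shall describe how many people restarted statin therapy within the first 6 months, 7–12 months and 12 or more months". The same sentence names Kaplan-Meier as the estimator. For censoring, the text refers to a Study design section. No section of the article carries that heading, and the list that fits is under Sample selection: "Patients will be followed up until the earliest of: death; deregistration with the practice; last upload of computerised data". Death is therefore handled like an administrative end of follow-up. The article mentions no competing-risk method.

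**Stopping.** Under Statistical analysis, the main measure is a rate: "the rate of discontinuation will be assessed by dividing the number of incident stoppers by the number of person-years". Numbers of stoppers and descriptive proportions by timing of the last prescription are also reported. Kaplan-Meier is used to "graphically summarise the data using Kaplan-Meier curves", and for the survivor function, median duration, curves by covariate and log-rank comparisons.

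**Other features that matter here.** Inclusion criteria require "at least 1 year of follow-up—calculated from their first statin prescription in the study period", so nobody in the main cohort can die in the first year. Primary prevention patients have a further exit: "Patients without CVD at the baseline date will be followed up until the time of a CVD diagnosis".

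**The concern.** How many people restarted is a statement about what happened to real patients. Kaplan-Meier with deaths censored answers a different question: what share would restart if nobody died and those who died had gone on restarting at the same rate as survivors. The section therefore fixes an estimator that does not match the quantity it promises.

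The cohort enters at ages 25 to 84, includes people with established cardiovascular disease and can be followed for many years, so deaths after stopping will not be rare. If too many stoppers are reported to resume treatment, discontinuation looks more temporary than it is. That bears on the study's interest in patients left at raised cardiovascular risk.

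**Working it through.** The document states no Kaplan-Meier proportion, stopping hazard, restart hazard or mortality, so there is no figure of the plan's own to reproduce. The direction of the bias follows from the method. Its size is illustrated on assumed constant yearly hazards.

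**Inputs from the document**
- Death ends follow-up (Sample selection) and is carried into the restart analysis (Additional analyses).
- Longest possible follow-up: 1 January 2002 to 30 September 2014 is 12.74 years, for patients entering on the first day only. Follow-up after stopping is shorter.
- No deaths in year 1 after the first prescription (Inclusion criteria).

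**Formulas** (event hazard *l*, death hazard *m*, time *t* in years)
- Kaplan-Meier complement: 1 − exp(−*l t*)
- Cumulative incidence with death competing: *l*/(*l*+*m*) × [1 − exp(−(*l*+*m*) *t*)]

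The first is never below the second, and the gap grows with *t* and with *m*.

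**Restarting, assumed *l* = 0.30, *m* = 0.04**

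| Time since stopping | 1 − Kaplan-Meier | Cumulative incidence | Gap (points) |
|---|---|---|---|
| 6 months | 1 − exp(−0.15) = 13.9% | 0.30/0.34 × [1 − exp(−0.17)] = 13.8% | 0.1 |
| 12 months | 1 − exp(−0.30) = 25.9% | 0.30/0.34 × [1 − exp(−0.34)] = 25.4% | 0.5 |
| 5 years | 1 − exp(−1.5) = 77.7% | 0.30/0.34 × [1 − exp(−1.7)] = 72.1% | 5.6 |
| 10 years | 1 − exp(−3.0) = 95.0% | 0.30/0.34 × [1 − exp(−3.4)] = 85.3% | 9.7 |

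The share placed in the band of 12 or more months, read at 10 years, is 95.0 − 25.9 = 69.1% by Kaplan-Meier and 85.3 − 25.4 = 59.9% by cumulative incidence.

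As a check on coherence at 10 years, the share dead without restarting is 0.04/0.34 × [1 − exp(−3.4)] = 11.4%, and the share alive and not restarted is exp(−3.4) = 3.3%. With the cumulative incidence these add to 85.3 + 11.4 + 3.3 = 100%. With the Kaplan-Meier figure they add to 109.7%.

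**Range.** With restart hazards of 0.10, 0.30 and 0.70 and death hazards of 0.02 to 0.15 per year, the gap is at most 1.0 point at 6 months, 0.1 to 3.2 at 12 months, 1.7 to 18.0 at 5 years and 2.8 to 29.1 at 10 years.

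**Limit of the constant-hazard model.** By the outcome definition, a stopper has no prescription in the first 90 days, so restarting cannot begin at once. If both clocks are started about 0.25 years later, the gap at 5 years uses *t* = 4.75: 1 − exp(−1.425) = 75.9% against 0.30/0.34 × [1 − exp(−1.615)] = 70.7%. That is a gap of about 5 points, much as before.

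**Stopping, overall curve only.** Assume stopping at 0.10 per year and death at 0.05 per year, with deaths allowed only after year 1.
- Year 1: both methods give 1 − exp(−0.10) = 9.5%, so there is no gap.
- 10 years, Kaplan-Meier: 1 − exp(−1.0) = 63.2%.
- 10 years, cumulative incidence: 0.0952 + 0.9048 × (0.10/0.15) × [1 − exp(−0.15 × 9)] = 54.2%.
- Median: Kaplan-Meier gives ln 2/0.10 = 6.9 years. Half the patients have actually stopped when 0.0952 + 0.6032 × [1 − exp(−0.15(*t* − 1))] = 0.5, which is *t* = 8.4 years.

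**The case against.** The strongest reply is that little of the study depends on this. The stated aim is to report rates of stopping. Those are events per person-year, supported by Cox hazard ratios, and neither is made invalid by censoring deaths. Restarting is an additional descriptive analysis, and two of its three bands lie within the first year, where the gap is small even at high mortality. The 1-year follow-up rule reduces it further for patients who stop early, because it shields them from death until that year is over. Kaplan-Meier also has a legitimate reading, conditional on staying alive, and it deals properly with deregistration and end of data. All of this stands. It confines the point to the open-ended last band and to how the figures are described.

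A reader might infer more than the text supports, in two ways.

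- *That the proportions who stop are taken from Kaplan-Meier.* No passage says so. Stopping is reported as counts, person-year rates and descriptive proportions by time of last prescription, and the Kaplan-Meier sentence concerns a graph.
- *That Kaplan-Meier curves compared across age or morbidity groups mix stopping with mortality.* It is the other way round. Under independent censoring the Kaplan-Meier curve does not depend on the death rate. With stopping at 0.10 per year it shows 63.2% at 10 years whether death after year 1 runs at 0.01 or 0.08 per year. The cumulative incidence would be 61.2% and 49.8%, so groups with higher mortality would look more persistent. For covariate comparisons the planned curves match the log-rank tests and should be kept.

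**Conclusion.** The point holds for restarting. Additional analyses names an absolute quantity and fixes an estimator that overstates it, because death is censored and no competing-risk method is given. The direction is certain. The size is not, because the document gives no restart rate or mortality. On the central assumption (0.30 and 0.04 per year, constant) it is 0.5 points or less within 12 months, 5.6 points at 5 years and 9.7 points at 10 years. The later figures apply only to patients who stopped early enough to be followed that long.

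For stopping, the point is conditional. It applies only if the overall curve or the median duration is presented as the share of patients who actually stop. It then amounts to about 9 points at 10 years (63% v 54%) on assumed rates of 0.10 and 0.05, and nothing in year 1. The person-year rates, Cox model, log-rank tests and covariate curves are not affected.

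Exit at a cardiovascular diagnosis in the primary prevention group is a separate matter. Such a patient can still restart, so censoring there is a choice of definition and not the error described here.

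**What to change.** - **Restarting:** replace the Kaplan-Meier estimates with cumulative incidence (Aalen-Johansen), treating death as a competing event and keeping deregistration, last upload and study end as censoring. Show the share who died without restarting beside the three bands, and state the time horizon at which the last band is read.
- **Stopping:** for the overall curve and median duration, either add the corresponding overall cumulative incidence or label the curve and median as conditional on staying alive.
- **Leave unchanged:** person-year rates, the Cox model, log-rank tests and covariate Kaplan-Meier curves, described as cause-specific.
- **Cross-reference:** point the restart analysis to Sample selection for its censoring rules, and say there how a cardiovascular diagnosis is handled after stopping.

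The cost is a change of wording and one extra estimator. Death is already recorded as an exit event, so no data need be added. Long-term restart percentages will come out somewhat lower, and comparison with any published Kaplan-Meier figures will need a sentence of explanation.

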### Outcome

The outcome will be defined as a discontinuation of statin use if there are no prescriptions within the 90 days following the expected finishing date of a prescription. The first such event will be considered as an outcome, and further prescriptions will not be used in the analysis of discontinuation. A 90-day exposure window has been used in other CPRD studies^29^
^30^ because it is the longest prescription length that can be issued in the UK. The date of the outcome will be defined as the expected finishing date of the prescription.

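### Discontinuation rates by term of use group patients by a near-copy of the outcome time, so a short/long contrast appears even when none exists

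*Protocol article*

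**What the plan says.** All references are to the protocol article.

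- **Statistical analysis, rate.** The discontinuation rate is obtained by "dividing the number of incident stoppers by the number of person-years".
- **Statistical analysis, grouping.** Because different rates are expected, users are divided in two. One group is "short-term (less than 12 months between the first and the last prescription"; in the other group that interval exceeds 12 months. For the two groups the authors announce: "we shall calculate rates by term of use".
- **Outcome, event.** A patient has stopped if there are "no prescriptions within the 90 days following the expected finishing date of a prescription". Only the first such gap counts, and "further prescriptions will not be used in the analysis of discontinuation".
- **Outcome, date.** "The date of the outcome will be defined as the expected finishing date of the prescription".
- **Inclusion criteria.** Patients need at least two statin prescriptions in the study period and at least 1 year of follow-up from the first one.

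**The concern.** The labels short-term and long-term are attached to people, not to stretches of person-time, and they are known only once follow-up is over. For a stopper, the interval from first to last prescription is the time to the outcome less the length of one prescription. The plan therefore stratifies a rate by its own outcome.

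Two things follow.

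- **Short-term group.** Everyone has at least a year of follow-up, so a patient whose last prescription falls before 12 months has usually stopped. The group's rate is then close to the inverse of its mean time on treatment, whatever the underlying hazard.
- **Long-term group.** Its members must have been prescribed past 12 months, so their first year is event-free by selection but still counts in the denominator.

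The plan says that it expects the two rates to differ, and this calculation will show a difference even if stopping is equally likely at all times. A reader would naturally take the contrast as evidence that the risk of stopping collapses after the first year.

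**Working it through.** The article gives no figure for these rates, so there is none to reproduce. The check asks what the planned calculation returns when the truth is known and contains no early/late difference.

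**1. Short-term group in closed form.** Take a constant hazard h per person-year and everyone followed for a year. Ignore prescription length, so that short-term means stopped before 1 year.

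- Events per starter: 1 − e^(−h)
- Person-years per starter: (1 − e^(−h))/h − e^(−h)
- Rate: the first divided by the second

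At h = 0.1: 0.0952 / 0.0468 = 2.03 per person-year. At h = 0.7: 0.5034 / 0.2226 = 2.26. The true hazard rises sevenfold and the short-term rate rises by 11% (2.26/2.03). The rate carries almost no information about the hazard.

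**2. Simulation under the plan's rules.**

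*From the article:* about 600 000 starters; entry 1 January 2002 to 30 September 2013 and end of follow-up 30 September 2014, giving 1 to 12.75 years of potential follow-up; at least 1 year of follow-up; at least two prescriptions; 90-day gap; outcome at the end of the last prescription's supply.

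*Assumed, because the article gives no values:* constant hazard h of 0.1, 0.2, 0.4 or 0.7 per person-year; prescription length L of 28, 56 or 90 days; other exit at 6% per year; uniform entry.

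*Formulas:* the chance of stopping at each prescription is 1 − exp(−hL/365.25). A patient who stops after k prescriptions has outcome time kL and first-to-last interval (k − 1)L. The event counts if 90 days fit between kL and the end of follow-up.

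| L (days) | h | Stoppers among short-term | Short rate | Long rate | Ratio, planned grouping | Year-1 rate | Later rate | Ratio, person-time split |
|---|---|---|---|---|---|---|---|---|
| 28 | 0.1 | 90% | 1.398 | 0.072 | 19.5 | 0.091 | 0.094 | 0.97 |
| 28 | 0.2 | 95% | 1.531 | 0.134 | 11.4 | 0.180 | 0.189 | 0.96 |
| 28 | 0.4 | 97% | 1.642 | 0.235 | 7.0 | 0.356 | 0.376 | 0.95 |
| 28 | 0.7 | 98% | 1.751 | 0.345 | 5.1 | 0.611 | 0.657 | 0.93 |
| 56 | 0.1 | 89% | 1.244 | 0.071 | 17.5 | 0.076 | 0.096 | 0.80 |
| 56 | 0.2 | 94% | 1.358 | 0.132 | 10.3 | 0.150 | 0.191 | 0.79 |
| 56 | 0.4 | 97% | 1.440 | 0.231 | 6.2 | 0.294 | 0.385 | 0.76 |
| 56 | 0.7 | 98% | 1.512 | 0.337 | 4.5 | 0.501 | 0.674 | 0.74 |
| 90 | 0.1 | 74% | 0.804 | 0.068 | 11.8 | 0.072 | 0.093 | 0.77 |
| 90 | 0.2 | 85% | 0.960 | 0.125 | 7.7 | 0.141 | 0.183 | 0.77 |
| 90 | 0.4 | 92% | 1.077 | 0.215 | 5.0 | 0.270 | 0.361 | 0.75 |
| 90 | 0.7 | 95% | 1.158 | 0.307 | 3.8 | 0.452 | 0.610 | 0.74 |

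Rates are per person-year. With 7% yearly exit instead of 6%, the planned grouping gives ratios of 3.8 to 19.4 and 73% to 98% stoppers among short-term users.

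**3. Where the long-term rate goes wrong.** Take L = 28, h = 0.2. In that run 50.1% of long-term users stop, so they contribute 0.501/0.134 = 3.74 person-years each. Taking off the event-free first year leaves 2.74, and 0.501/2.74 = 0.183, close to the later rate of 0.189. Most of the shortfall is that first year.

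**4. Why the split ratio is below 1.** The two-prescription rule bars stopping after the first prescription. With 90-day prescriptions, four finish dates fall in the first year (360 days) and one is barred, so about 3/4 = 0.75 of the hazard remains, near the 0.74 to 0.77 in the table. With 28-day prescriptions, one of thirteen is barred and the effect is small.

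**The case against.** The strongest reply is about weight. These rates are one sentence in a paragraph of descriptive statistics, and no test, hazard ratio or sample-size statement uses the grouping. The timing of stopping is described validly elsewhere: the Kaplan-Meier curves and survival-time function show it directly, and Additional analyses reruns the main model for stopping before and after the end of year 1. All of this stands and lowers the severity. It does not rescue the rates, which would still be published with the contrast built in.

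A second reply is that the size rests on assumed inputs. That also stands. A single ratio should not be quoted, and short-term users are not all stoppers: with 90-day prescriptions and a low hazard about a quarter are not.

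Two stronger readings are tempting, and the document does not support them.

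- **Last prescription in the whole record.** A reader might infer that the grouping uses prescriptions after a restart, so that someone who stops early and restarts counts as long-term, in conflict with the Outcome section. The Statistical analysis section does not say so, and the Outcome section states that "further prescriptions will not be used in the analysis of discontinuation", which points to the last prescription before the first gap. Any figure for early stoppers mislabelled in this way would also need a restart share that the article does not give. On that reading the grouping would still depend on the future, so the problem would not go away.
- **The second year-1 rerun.** A reader might infer the same fault where Additional analyses plans "in the second removing all patients who did discontinue before the end of year 1". That section reruns the main analysis, which is the Cox model. With year-1 stoppers removed, no events occur before month 12, so every risk set lies after it. The hazard ratios are the same whether the clock starts at first prescription or at month 12.

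**Conclusion.** The point holds for the rates by term of use in the Statistical analysis section, and only for those. As written, the calculation conditions on the outcome and yields a large short/long contrast when none exists: a rate ratio of about 4 to 19, with 73% to 98% of short-term users being stoppers. This rests on a constant hazard of 0.1 to 0.7 per person-year, prescriptions of 28 to 90 days and yearly exit of 6% to 7%, none of which the article states. The direction was the same in all scenarios; the size is not to be taken as a prediction.

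The overall rates, the rates by baseline factors, the main Cox model, the Kaplan-Meier curves and the year-1 reruns are unaffected. The severity is should-fix: an error in a secondary descriptive measure that would mislead readers on timing but leaves the main inference intact.

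**What to change.** Replace the rates by term of use with rates by time since first prescription, splitting each patient's person-time at 12 months:

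- **Year 1:** discontinuations in the first 12 months over person-years in the first 12 months, for all patients.
- **After year 1:** later discontinuations over later person-years, for patients still on treatment and under follow-up at 12 months.

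Add a note that the two-prescription rule lowers the year-1 rate somewhat, by little for 28-day prescriptions and by up to about a quarter for 56- to 90-day ones under the assumptions above. The planned sensitivity analysis that admits patients with a single prescription could be tabulated in the same way.

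The cost is one sentence of text and a standard episode split in the Stata software already planned. No new data are needed and no other analysis changes.

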## Methods and analysis

### Data source

We will use data from 664 UK general practices contributing to the CPRD (http://www.cprd.com). The practices are spread across the UK, and their registered patients have been shown to be representative of the general population.^38^ Data are routinely collected and the recorded information includes demographics, patient characteristics, clinical diagnoses, symptoms and prescribed medications. The database has been validated using other sources of information in the UK and has been used for similar studies for statin discontinuation.^29^
^30^

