### Covariates

To describe the cohort and explore factors associated with the risk of discontinuation, we will consider the following covariates in six major groups. First, demographics will include age (<45; 45–54; 55–64; 65–74; 75–84 years), sex, ethnicity (Caucasian or not recorded, Indian, Pakistani, Bangladeshi, other Asian, Black African, Black Caribbean, Chinese, other ethnic group) and socioeconomic status as measured by the Townsend deprivation score in quintiles. Second, clinical values will include smoking status (non-smoker; ex-smoker; light smoker: <10 cigarettes/day; moderate smoker: 10–19 cigarettes/day; heavy smoker: 20+cigarettes/day; not recorded), body mass index (BMI) in kg/m^2^ (<25; 25–29.9; 30–34.9; 35+, not recorded), systolic blood pressure and cholesterol/high-density lipoprotein (HDL) ratio. Third, chronic diseases will include rheumatoid arthritis, chronic renal disease, liver disease, atrial fibrillation, treated hypertension, cancer, heart failure, diabetes and dementia. Fourth, genetic characteristics will include family history of premature coronary heart disease and diagnosis of familial hypercholesterolaemia. Fifth, other medications will include use of aspirin, use of anticoagulants and—as a proxy for comorbid conditions—the number of different types of medicines having systemic effect and associated with British National Formulary^39^ categories (in each case, at least one prescription in the last year before the entry date). Finally, only for patients in the primary prevention group, their 10-year cardiovascular risk as calculated by the QRISK2–2014 score (banded <5%; 5–9%; 10–14%; 15–19%; 20–24%; 25%+).

For clinical values, the most recently recorded value prior to or at the cohort entry will be used. Chronic diseases will be considered if they were recorded at or before the baseline. For the main analysis, we will use practice-based Townsend deprivation scores as these are available for the whole cohort. We will run an additional analysis on the subset of practices that have consented to link their data to Townsend scores at patient level.

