To explore the risks of statin discontinuation associated with the covariates, a Cox regression analysis will be undertaken. The model will include age, sex, ethnic group, deprivation quintile, calendar year at the entry to the cohort, baseline CVD risk and the type of statin prescribed at the baseline. Practices might differ in their prescription patterns, so we will account for clustering by practice. We shall calculate the adjusted HRs for baseline characteristics listed above: clinical values; chronic diseases; family history; use of other medications.

The proportional hazards assumption will be checked by using a log-log plot of survival for each variable. Variables which violate the assumption will be included into the model as a stratification factor. If clinically similar variables or categories (for smoking and ethnicity) are associated with similar risks, they will be combined. For continuous variables, recorded values will be used. For non-linear risk associations, fractional polynomials will be used if appropriate.^40^

As BMI, smoking status, systolic blood pressure and cholesterol/HDL ratio may be important patient characteristics but have non-negligible numbers of missing data, multiple imputation will be used to replace missing values.^41^ Five imputed data sets will be created, using multiple chained equations, and Rubin's rules will be used to combine effect estimates and SEs to allow for uncertainty due to imputing missing values. Calendar year; statin stopper status; log of survival time; age; years of records; potentially important characteristics; and type, dose and cumulative exposure to statins will be included in the imputation model.^42^

The main analyses will be run using the multiply imputed data. The least complete data are expected to be for cholesterol/HDL ratio, but information about this test is expected to be important for patient adherence. To ensure the robustness of our findings, we shall also run a sensitivity analysis including only patients with complete data.

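### Clustering by practice is to be accounted for by an unnamed method that cannot be practice stratification; a within-practice sensitivity analysis for statin type would be a cheap improvement

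*Protocol article*

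**What the plan says.** All places are in the protocol article.

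- **Practice (Statistical analysis).** "Practices might differ in their prescription patterns, so we will account for clustering by practice". The method is not named.
- **Model terms (Statistical analysis).** "The model will include age, sex, ethnic group, deprivation quintile, calendar year at the entry to the cohort, baseline CVD risk and the type of" (cut short here; the last term is the baseline statin). Practice is not among the listed terms.
- **Deprivation (Covariates).** "For the main analysis, we will use practice-based Townsend deprivation scores as these are available for the whole cohort". Patient-level scores are used only in an additional analysis of the practices that consented to linkage.
- **Stratification (Statistical analysis).** It is foreseen only where proportional hazards fail: "Variables which violate the assumption will be included into the model as a stratification factor".
- **Outcome (Outcome).** "The outcome will be defined as a discontinuation of statin use if there are no prescriptions within the 90 days following" (cut short here; the 90 days run from when a prescription should have ended). The outcome is therefore itself derived from prescribing records.
- **Sensitivity analyses.** There are four: patients with a single prescription, complete cases, a 12-month gap, and follow-up restricted to 5 years. None concerns practice.

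**The concern.** The reason given for the clustering adjustment is that prescribing differs between practices. Such differences have two consequences. Patients in one practice resemble each other, which affects standard errors. Practice also helps to determine which statin a patient starts, which affects the HR if practice influences discontinuation as well.

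The second route is plausible here, because a discontinuation is a gap in issued prescriptions. A practice's recall and repeat-prescribing habits could shape that gap. A correction to the variance alone does nothing about this route.

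The comparison between statins matters to the study. The Introduction asks whether stopping rates differ by statin type, simvastatin is the reference drug, and the sample size section is built on HRs against simvastatin. A practice difference read as a drug difference would carry a narrow interval, because the cohort is very large.

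**Working it through.** **1. The effect that the study is sized on.** Schoenfeld events, two-sided 1%, 90% power, 1:1 allocation: 4 × (2.5758 + 1.2816)² / (ln HR)².
- HR 0.9 gives 5362 and HR 0.8 gives 1196, as stated.
- HR 1.1 gives 6552, so 5362 belongs to HR 0.9 only. Nothing below depends on this.

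**2. Which clustering methods fit the plan.**
- Practice stratification or practice fixed effects: a practice-based Townsend quintile does not vary within practice, so its HR cannot be estimated. The main model lists it, so these are effectively ruled out.
- Cluster-robust variance: the point estimate is that of the ordinary Cox model and only the standard error (SE) changes.
- Shared frailty: it assumes practice effects independent of the covariates. If they correlate with statin choice, the bias is reduced but not reliably removed.

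**3. Possible size of the bias.** The documents give no between-practice SDs or correlations, so every input here is an assumption, to be read as what remains after Townsend score and entry year. Neither of these covariates was simulated. Both simulations used 664 practices ("We will use data from 664 UK general practices contributing to the CPRD") with 225 patients each and a true statin HR of 1.00. The practice size is close to the CVD-group average: 600 000 / 4 / 664 ≈ 226.

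*Simulation A* (comparator share 20% on average, Weibull shape 0.6, staggered censoring, 12 replicates):

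| SD of practice share | SD of practice log hazard | Correlation | Unstratified HR | Stratified HR |
|---|---|---|---|---|
| 12–15 points | 0.20 | 0.3 | 1.040 and 1.042 | 0.998 and 1.000 |
| 15 points | 0.25 | 0.5 | 1.109 | 0.998 |
| – | – | 0 | 1.001 | 0.998 |

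*Simulation B* (practice SD of 1.0 on the logit of non-simvastatin use, share about 0.28, constant hazard, 5 replicates), unstratified HR:

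| SD of practice log hazard | Correlation 0 | 0.2 | 0.4 |
|---|---|---|---|
| 0.2 | 0.999 | 1.039 | 1.069 |
| 0.3 | 0.999 | 1.053 | 1.098 |
| 0.4 | 0.999 | 1.079 | 1.137 |

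The stratified HR in B lay between 0.995 and 1.005 throughout.

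**4. Hand check.** Log bias ≈ correlation × SD(share) × SD(log hazard) / [p(1 − p)]. For the upper setting of A this is 0.5 × 0.15 × 0.25 / 0.16 = 0.117, or HR 1.12, against 1.109 simulated. For the lower setting, 0.3 × 0.12 × 0.20 / 0.16 = 0.045, or HR 1.05, against 1.04.

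**5. Against the study's precision.** With 5362 events at 1:1, the model-based SE is 2/√5362 = 0.027. A false HR of 1.04 lies ln(1.04)/0.027 ≈ 1.4 SE from the null and one of 1.10 about 3.5 SE. The 1% cut-off is 2.58. A cluster-robust SE would be somewhat larger.

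**6. Price of stratifying.** Within-practice exposure variance is p(1 − p) − SD(share)². At p = 0.20, the SE ratio is √[0.16 / (0.16 − 0.12²)] = 1.05 for an SD of 12 points and √[0.16 / (0.16 − 0.15²)] = 1.08 for 15 points. Simulation A gave 1.05 to 1.07. Wider variation between practices would cost more.

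**7. Information within practices.** The average is 600 000 / 664 ≈ 904 patients per practice, of whom about 226 have CVD. Fluvastatin, at under 1% of exposure, has fewer than about 2.3 CVD patients per practice.

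**The case against.** A reader might infer that the plan handles practice only through the standard errors and that the statin-type HR is therefore confounded. The documents do not support this, for four reasons.

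- **The method is unnamed.** A frailty fits the wording as well as a robust variance does, and a journal article may leave the technical form to a fuller plan. This stands as far as it goes. It does not rescue practice stratification, which the practice-based Townsend term excludes.
- **Confounding needs a second link.** Practices that prefer a statin must also differ in persistence, given the covariates. The plan says only that prescribing may differ. This stands: at zero correlation there is no bias, and an HR of 1.10 or more needs several sizeable inputs together.
- **Some practice and period differences are adjusted for**, through the practice-level Townsend score and entry year. This stands in part, since neither measures recall or repeat-prescribing habits.
- **The model is exploratory.** The plan says "To explore the risks of statin discontinuation associated with the covariates, a Cox regression analysis will be undertaken", and an overall adjusted association is a legitimate target. This stands as a reason to keep the planned model as the main one. It is no reason against showing the within-practice comparison as well, because readers will take an adjusted statin-type HR as a difference between drugs.

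The argument concerns statin type. It does not by itself justify stratified results for every other patient factor.

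**Conclusion.** The point holds as a cheap improvement. The plan's own deprivation term confines the clustering adjustment to methods that do not guarantee removal of practice-level confounding of the statin-type HR, and no sensitivity analysis covers this. The apparent HR under no drug effect runs from 1.00 to 1.14, wholly on assumed inputs: practice log-hazard SD 0.2 to 0.4 and correlation 0 to 0.5, with the 1.14 at SD 0.4 and correlation 0.4. At the top of that range the bias matches or exceeds the 0.9/1.1 effect; at the bottom it is nil. The simulations show that such a bias is possible and that stratification removes it. They do not show that it is present in these data.

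**What to change.** 1. Name the clustering method (robust variance or shared frailty).
2. Keep the planned model as the main analysis and as the source of the practice-based Townsend HR.
3. Add a sensitivity analysis for statin type: the same Cox model stratified by practice, without the practice-based Townsend term, separately for primary and secondary prevention. Report its statin-type HRs beside those of the main model.
4. State how the pair will be read. Agreement supports a drug difference; a shift towards 1 in the stratified column points to practice.

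The cost is one option in the Cox command, one more results column, and intervals about 5 to 8% wider for common statins if the share varies between practices by 12 to 15 points around 20%. That price was not worked out for statins with a small share. For fluvastatin in the CVD group there is little within-practice information, and the report should say so.
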